### Aims of the study

Primary objective: To determine the time course of the levels of circulating EPCs (CD133/CD34), SDF-1a, and HIF-1 in septic patients undergoing major abdominal surgery.

Secondary objective 1: To investigate the relationship between CD133/CD34, HIF-1, and SDF-1a.

Secondary objective 2: To investigate the relationship between CD133/CD34, HIF-1, SDF-1a, and the outcome of sepsis and septic shock patients treated with standard conventional therapy alone (CT) or with the addition of extracorporeal hemoperfusion therapy (HCT).

In this trial, we hypothesize that levels of CD133/CD34, HIF-1, and SDF-1a will increase in septic surgical patients as a consequence of impaired tissue perfusion and cellular hypoxia. Our hypothesis is that the stimulation of hypoxia-related factors, like SDF-1a and HIF-1, could be the primary step in the stimulation of BM stem cells. Furthermore, we assume that surviving septic patients will show higher levels of EPCs, HIF-1, and SDF-1a.

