## Methods/design

### Recruitment

This prospective observational clinical trial is designed to target postoperative patients undergoing major abdominal surgery and healthy volunteers at University Hospital Foggia. Participants who meet pre-specified eligibility criteria (Table 1) and provide written informed consent will be enrolled in the study.

**Table 1 Tab1:** Eligibility criteria

Inclusion criteria	Exclusion criteria
Caucasian Over 18 years of age	When it is impossible to collect blood samples (organizational reasons or because of emergencies regarding the health of the patient)
	Pregnant patients
	Organ transplantation
	Palliative care
	Metastatic cancer patients

Detailed information on the benefits and risks of taking a blood sample will be provided to study candidates. Human blood samples and therapies will be acquired in accordance with institutional guidelines. All patients will be managed by applying standard protocols, following current guidelines and recommendations. The diagnosis of sepsis and septic shock will be made according to the new definitions [17].

This study is to be performed in accordance with the *World Medical Association Declaration of Helsinki: Ethical principles for medical research involving human subjects* (WMA 20 2013) [18], the *International Ethical Guidelines for Biomedical Research involving Human Subjects* (CIOMS 2002) [19], and the *ICH Harmonised Tripartite Guideline: Guideline for good clinical practice* (ICH 1996) [20].

The study has been approved by the local research ethics committee (Comitato Etico of Ospedali Riuniti, Foggia, Italy, 69/CE/2015). The trial has been registered with ClinicalTrials.gov (NCT02589535). We adhered to the SPIRIT statement (Additional file 1).

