### Study design

Each day, the anesthesiologist in the operating room and the on-call anesthesiologist will alert the principal investigator to potential eligible patients. Participants included in the trial will be divided into two groups:Group C: Postoperative non-septic patients in an emergency surgical ward (control group)Group S: Postoperative septic shock patients in an ICU

Using a computer-generated sequence of numbers, patients in group S will be randomly assigned to receive either conventional therapy for septic shock alone (CT) as per the Surviving Sepsis Campaign guidelines (S1) or standard therapy plus extracorporeal hemoperfusion therapy (HCT) with polymyxin B-immobilized polystyrene-derived fibers to remove endotoxins from the blood (S2) [21]. Healthy volunteers (group H) will be recruited from among staff members of the University Hospital Foggia (Figs. 1 and 2).

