### Blood sampling

PB samples will be collected in sterile evacuated blood collection tubes with anticoagulant ethylenediaminetetraacetic acid (EDTA; 3 ml) at the following time points:preoperatively (T0), at 24 h (T1), 72 h (T2), 7 (T3), and 10 (T4) postoperative days in groups S and CT0 in group H

The absolute numbers of leukocytes and lymphocytes in PB will be determined at the same time with an automatic cell counter (Cell-Dyn 3500, Abbott Diagnostics, Santa Clara, CA, USA). Peripheral whole blood samples (100 μl) will be used for fluorescence-activated cell sorting (FACS) analysis, and the plasma samples will be collected and stored at −80 °C.

Biochemical tests will be determined daily, according to the routine procedure in the surgical ward and ICU, and performed in the laboratories at University Hospital Foggia, according to the institutional guidelines.

Demographic, anamnestic, clinical, and laboratory data will be recorded.

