### Statistical analysis

The power analysis suggested that a sample size of 30 patients per group is required to detect a higher percentage of total circulating EPCs (CD133+/CD34+ cells as a percentage of all myelomonocytic cells) in septic patients vs ICU controls (assuming α = .05 and power = .95) [22]. A sample size of three patients per group is required to detect higher SDF-1 levels in the septic vs control groups (assuming α = .05 and power = .95) [10]. This number is increased to 33 per group to allow for a 20% drop-out rate.

The normality of the distribution will be assessed by the Shapiro–Wilkinson test. If the data are normally distributed, they will be expressed as mean (± standard deviation). The data will be analyzed using the repeated measurements analysis of variance. Differences between the groups at each time point will be examined post hoc using an independent sample *t* test. A paired sample *t* test will be used to detect changes within the groups. The level of statistical significance was chosen as *P* < .05. The statistical analysis will be performed with the Statistical Package for the Social Sciences (SPSS Inc., Chicago, IL) version 15.0 for Windows.

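### Septic (S) and ward control (C) patients are not randomised or matched, yet their markers are compared without covariates, so pre-existing differences can mix into the S–C contrast

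*Protocol article*

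**What the plan says.** - **How the groups arise.** The Study design section defines the control group as "Group C: Postoperative non-septic patients in an emergency surgical ward (control group") and the septic group as "Group S: Postoperative septic shock patients in an ICU". Membership follows from the patient's condition and ward.
- **What is randomised.** Only the treatment split within group S: "patients in group S will be randomly assigned to receive either conventional therapy for septic shock alone (CT") or the same with hemoperfusion.
- **Eligibility.** Table 1 is broad: Caucasian, over 18, and a few exclusions. No matching or stratification of S and C is described anywhere in the article.
- **Hypothesis.** The Aims section expects that "levels of CD133/CD34, HIF-1, and SDF-1a will increase in septic surgical patients as a consequence of impaired tissue perfusion and cellular hypoxia".
- **Analysis.** The Statistical analysis section names a repeated-measures ANOVA, paired t tests within groups, and between groups: "Differences between the groups at each time point will be examined post hoc using an independent sample *t* test". No covariate is named.
- **Sample size.** The same section rests it on a septic-versus-control difference, with 30 per group, α = .05 and power .95.
- **Data available.** The Blood sampling section states: "Demographic, anamnestic, clinical, and laboratory data will be recorded". The analysis section gives these data no role.

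**The concern.** An independent-sample t test takes no covariates, so whatever separates the two groups goes into the mean difference. Patients in septic shock in intensive care and non-septic patients on an emergency surgical ward could differ in age, sex or chronic disease before the operation. If such a characteristic is also related to EPC, HIF-1 or SDF-1a levels, its contribution cannot be told apart from that of sepsis.

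What is at stake is the reading given in the Aims, where the rise is a consequence of impaired perfusion and hypoxia. Confounding could produce an apparent rise where sepsis causes none, or hide a real one. The characteristics needed to reduce this are already being recorded.

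**Working it through.** **1. The plan's own figure.** Inputs from the Statistical analysis section: n = 30 per group, α = .05, power = .95. No effect size or SD is given, so the 30 cannot be reproduced. It can only be turned into the difference that it implies. With a noncentral t distribution on 2 × 30 − 2 = 58 degrees of freedom, the standardised difference giving 95% power is 0.947 SD two-sided, or 0.860 SD one-sided. The section does not state sidedness. Two-sided is used below.

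**2. Bias from one omitted characteristic.** In SD units of the marker:

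bias b = (S–C gap on the characteristic, in SD) × (slope of the marker on it, in SD per SD)

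The article gives neither term. Assumed range: gap 0.5 to 1 SD, slope 0.2 to 0.4.

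- Lowest: 0.5 × 0.2 = 0.10 SD
- Highest: 1 × 0.4 = 0.40 SD

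**3. Effect on a single time-point test.** With no sepsis effect, the t statistic has noncentrality b × √(n/2) = b × √15, and P < .05 needs |t| > 2.00. For b = 0.30, the noncentrality is 0.30 × 3.873 = 1.16. If the bias runs against a true difference of 0.947 SD, the noncentrality is (0.947 − b) × √15.

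| Assumed bias b (SD) | P < .05 with no sepsis effect | Power if the bias opposes a true 0.947 SD |
|---|---|---|
| 0 | 5.0% | 95% |
| 0.10 | 6.7% | 90% |
| 0.20 | 11.9% | 81% |
| 0.30 | 20.8% | 69% |
| 0.40 | 33.2% | 55% |

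**4. What adjustment does.** A simulation of 10,000 trials per setting used 33 per group, no sepsis effect, covariate–marker correlation 0.3 or 0.5, and a gap of 0.5 or 1.0 SD. These are also assumptions, and they reach a bias of 0.5 × 1.0 = 0.50 SD. The t test gave P < .05 in 9% to 52% of trials. With the covariate in the linear model the rate was 4.8% to 5.0%. This setting has one confounder, fully measured and linear, so it shows the best that adjustment can do.

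**The case against.** Several counter-arguments have weight.

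- **It is an omission that belongs in a full protocol or SAP.** The section never excludes covariates, and covariate lists are often placed elsewhere. This would succeed if the article had left the between-group method open. It names one, however, and that method cannot take covariates. A later plan that adjusted would depart from the published one.
- **The t test is valid for what it tests.** This stands. It correctly compares the means of two different populations. If septic and non-septic patients truly differ on a marker, for whatever reason, rejecting equality is no error. A reader might infer that the trial's type I error is 7% to 33%. The article does not support that: these rates are errors only against the causal reading in the Aims.
- **The study calls itself observational.** Recruitment says: "This prospective observational clinical trial is designed to target postoperative patients undergoing major abdominal surgery and healthy volunteers". The objectives speak of time course and relationships. This weakens any charge that a causal claim is promised, but the stated hypothesis is still worded as cause and consequence.
- **The primary objective is the time course in septic patients.** This also stands. The within-group paired tests address that question without group C, and a fixed characteristic with a constant effect over time cancels from a group-by-time contrast. The t tests at each time point, however, make no use of the T0 value.
- **Adjustment has a price.** Type of operation may be determined by the infection, so adjusting for it could remove part of the contrast of interest or leave little overlap. This is right, and it limits the fix.

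**Conclusion.** The point holds as a weakness in a stated method. The S–C contrast, on which the sample size rests, compares groups that are neither randomised nor described as matched, with an analysis that uses no covariates, while the hypothesis attributes the difference to sepsis physiology. Under an assumed bias of 0.10 to 0.40 SD, with 30 per group and two-sided .05, a single time-point test would give P < .05 in about 7% to 33% of trials with no sepsis effect. With the bias reversed, power for 0.947 SD would be about 90% to 55%.

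The bias range is an assumption. A reader might infer that S and C do differ in age, sex or comorbidity. The article shows no such difference, and both groups share one hospital, the same eligibility criteria and major abdominal surgery. Nor does the point reach the randomised S1 versus S2 comparison or the time course within septic patients. It should be corrected, but it does not invalidate the study.

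**What to change.** For S versus C only:

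1. Make the main between-group analysis of each marker a linear repeated-measures model with group, time, their interaction, and a short set of recorded pre-existing characteristics: age, sex and one comorbidity measure. Fix the set before any marker data are examined.
2. Take the time-point contrasts from that model, and report the independent t tests as supplementary.
3. Use type of operation in a sensitivity analysis at most, since it may follow from the infection.
4. Describe S–C differences as associations with septic status. Adjustment covers measured characteristics only and cannot separate sepsis from the setting of care.

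The cost is a sentence or two in the analysis section and a few degrees of freedom at about 30 per group, which is why the set must stay small. No new patients are needed, and the covariates come from data already planned for recording. The Trial status section reports recruitment as ongoing, so the choice could still be fixed ahead of the marker analysis.

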## Discussion

The proposed study is a prospective observational clinical trial designed to investigate in septic postoperative abdominal surgical patients: (a) levels of circulating stem cells, HIF-1, and SDF-1a; (b) the interrelationship among stem cells, HIF-1, and SDF-1a; and (c) the correlation of those factors with outcomes for septic postoperative abdominal surgical patients treated with CT alone or with HCT. The rationale is that a deep and integrated molecular understanding of sepsis at the system level will indicate which molecular processes need to be regulated to recover the innate immunity homeostasis.

A potential limitation is that blood samples will be not collected in those patients operated on as an emergency over night or when the laboratory is closed, since the HIF-1 analysis requires immediate collection-to-storage times of fresh blood samples [23].

Understanding the function of EPCs in sepsis and sepsis-related organ dysfunction may provide innovative diagnostic and therapeutic approaches for this devastating syndrome.

### Trial status

Patient recruitment is currently being undertaken.

## Abbreviations

BM: Bone marrow
CT: Conventional therapy alone
EPC: Endothelial progenitor cell
FACS: Fluorescence-activated cell sorting
HCT: Conventional therapy plus extracorporeal hemoperfusion therapy
HIF-1: Hypoxia inducible factor 1
ICU: Intensive care unit
PB: Peripheral blood
SDF-1a: Stromal-cell-derived factor 1a
